### Exclusion criteria

2.5

The exclusion criteria are as follows:

1.infertility caused by organic lesions of the reproductive system or male infertility;2.pregnant women or women in their lactation period;3.complicated with bleeding disorders (for example, thrombocytopenia with bleeding tendency, coagulation disorder), mental diseases (serious anxiety and depression, schizophrenia), malignant tumor, or serious organic diseases;4.history of radioiodine therapy or surgical intervention of the thyroid;5.use of immunosuppressants, immunostimulants, or drugs that interfere with the production, transport, and metabolism of thyroid hormones (e.g., corticosteroids, lithium, and amiodarone);6.participated in other clinical trials in the past 3 months.

### Sample size

2.6

Sample size will be decided by the primary outcome. The primary outcome of this study will be the mean change of TPOAb and TGAb from baseline to week 12. According to the results of our previous pilot study, titers of TPOAb was 253.86 ± 178.23 IU/ml in the acupuncture group and 318.98 ± 201.37IU/ml in the sham acupuncture group (TPOAb higher than 34IU/ml was the positive threshold of this research center). Considering participants recruited in the two groups are in a 1:1 ratio, the following formula was used to estimate sample size: 
[figure not shown]

With a 5% significance level (*α* = 0.05, two-sided) and 80% power (*β* = 0.2), at least 134 patients should be enrolled in each group and 284 total participants will be recruited to allow for a 10% dropout rate.

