### Primary outcome

6.1

The primary outcome in this trial is the titers of TPOAb and TGAb at baseline and at the 4th, 8th, and 12th week after randomization.

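### The 80% power is calculated for a between-group difference in TPOAb titers, not for the change to week 12 that the sample-size section names as the primary outcome

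*Protocol article*

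**What the plan says.** Section 2.6 (Sample size) opens with "Sample size will be decided by the primary outcome" and then defines that outcome: "The primary outcome of this study will be the mean change of TPOAb and TGAb from baseline to week 12". The pilot figures that follow are "titers of TPOAb was 253.86 ± 178.23 IU/ml in the acupuncture group and 318.98 ± 201.37IU/ml in the sham acupuncture group". No visit is attached to these titers. The section gives no baseline values, no mean or SD of change, no correlation between visits, and no figures for TGAb. It concludes that "at least 134 patients should be enrolled in each group" for a two-sided 5% level and 80% power.

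Section 6.1 (Primary outcome) describes the primary outcome as "the titers of TPOAb and TGAb at baseline and at the 4th, 8th, and 12th week after randomization". The Abstract names the titers of both antibodies as the primary assessment and lists the measurement weeks. Section 6.5 (Statistical analysis) plans a t test or nonparametric test for continuous variables. It also plans a repeated-measures analysis of both antibodies over four time points.

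**The concern.** A power statement describes the trial only if it refers to the quantity that will be tested. Section 2.6 names a change from baseline, but its inputs are titers with their cross-sectional SDs. The SD of a change depends on how strongly baseline and week-12 values are correlated, and it can be well above or well below the titer SD. The 80% therefore does not automatically carry over to the change.

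The wording in 6.1 adds a second difficulty. Titers at four visits do not say which between-group contrast is primary. Week-12 change, week-12 titer and the four-visit profile have different variances and can lead to different test results. If the choice stays open, it could be made after the data are seen.

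**Working it through.** **Inputs (section 2.6).** TPOAb titers 253.86 (SD 178.23) and 318.98 (SD 201.37) IU/ml; two-sided alpha 0.05; power 80%; 1:1 allocation. The sample-size formula is a figure missing from the text at hand, so the inputs it used are checked by reproducing its result.

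**Step 1: reproduce the plan's figure.**
- Difference: 318.98 − 253.86 = 65.12.
- Pooled SD: √((178.23² + 201.37²)/2) = 190.15. Standardised difference: 65.12/190.15 = 0.342.
- n per group = 2 × [190.15 × (1.960 + 0.842)/65.12]² = 133.85, rounded up to 134.

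This is the stated figure. The calculation was therefore done on titers and their cross-sectional SDs. The figures cannot sensibly be read as changes: the text calls them titers, and read as reductions they would favour sham.

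**Step 2: the same size applied to change from baseline.** The correlation rho between baseline and week 12 is not in the document, so it is varied. Assumptions: equal SD at both visits, and the same difference of 65.12.
- SD of change = 190.15 × √(2(1 − rho)). This equals the titer SD only at rho = 0.5.
- Power at n per group = Φ(65.12/(SD × √(2/n)) − 1.96). With n = 134, √(2/n) = 0.1222.
- Example, rho 0.3: SD of change 225.0, standard error 225.0 × 0.1222 = 27.5, ratio 65.12/27.5 = 2.37, power Φ(0.41) = 66%.

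**Step 3: the same size applied to week-12 titer adjusted for baseline.** Under the same assumptions the residual SD = 190.15 × √(1 − rho²), which never exceeds the titer SD.
- Example, rho 0.3: SD 181.4, standard error 22.2, ratio 2.94, power Φ(0.98) = 84%.

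| rho (assumed) | SD of change | n per group, change | Power at 134, change | n per group, baseline-adjusted | Power at 134, baseline-adjusted |
|---|---|---|---|---|---|
| 0 | 268.9 | 268 | 51% | 134 | 80% |
| 0.3 | 225.0 | 188 | 66% | 122 | 84% |
| 0.4 | 208.3 | 161 | 73% | 113 | 86% |
| 0.5 | 190.2 | 134 | 80% | 101 | 90% |
| 0.6 | 170.1 | 108 | 88% | 86 | 94% |
| 0.7 | 147.3 | 81 | 95% | 69 | 98% |
| 0.8 | 120.3 | 54 | 99% | 49 | >99% |

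Powers use the normal approximation. At 134 per group the noncentral t gives 79.8% for the titer comparison, so the choice of method does not matter here.

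**The case against.** The strongest reply has four parts.

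- **Titers are named elsewhere.** The Abstract and 6.1 both speak of titers, which is the kind of quantity that was powered, and only 2.6 speaks of change. Section 6.1 can be read as listing when titers are measured and 2.6 as giving the contrast. This has force. The pilot group titer is an input and is never declared an endpoint, so a reader who counts three competing primary endpoints goes too far. It does not settle the matter, because 2.6 itself says that the outcome which decides the size is the change.
- **The target difference is the same.** With randomised groups the expected baselines are equal, so the expected difference in change equals the expected difference in week-12 titer. This stands: the mismatch lies mainly in the SD. A reader might infer that the 65.12 reflects unequal pilot baselines. The document gives neither the pilot baselines nor the visit, so it neither supports nor excludes that.
- **No loss of power is shown.** A reader might infer that the trial is under-powered. The documents do not support this. The low figures arise only for an unadjusted change score with rho below 0.5. Above 0.5 the trial has more than 80% power for change.
- **Using titer SDs is a common and often cautious approximation.** It is cautious for a baseline-adjusted analysis, as step 3 shows. Section 2.6 does not state that analysis. For the mean change that it does state, the approximation is optimistic whenever rho is below 0.5.

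**Conclusion.** The point holds in a limited form. The 134 per group and the 80% power belong to a between-group difference in TPOAb titers. They are not shown to be the size and power for the mean change to week 12, although 2.6 says that this outcome decides the sample size. The primary outcome is also worded differently in 2.6 and 6.1.

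For an unadjusted change, power at 134 per group is about 66% at rho 0.3, 80% at 0.5 and 95% at 0.7. This assumes equal SDs at the two visits and a difference of 65.12. Since rho is not given, the size and direction of the error are both unknown. For the baseline-adjusted week-12 titer, the same assumptions give at least 80% at every correlation.

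These statements concern 134 evaluable women per group. Whether 284 recruited delivers that number after the stated dropout is a separate question. For TGAb, the other antibody named as primary, the document gives no sample-size input, so nothing can be said about its power.

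**What to change.** 1. State one primary contrast in the same words in the Abstract, 2.6 and 6.1: the between-group difference in week-12 titer, adjusted for baseline titer, with weeks 4 and 8 supportive. Name the same contrast in 6.5, so that it is clear which result of the repeated-measures analysis is primary.
2. Say in 2.6 that the power figure refers to TPOAb titers, and that for the baseline-adjusted analysis 134 evaluable per group is conservative.
3. If an unadjusted change score is kept instead, restate the power from the SD of change, or from the baseline-to-week-12 correlation, and give its source.
4. Leave TGAb with the status that the protocol gives it, and note that no power is given for it.

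Items 1, 2 and 4 cost only rewording. The baseline titer is already collected, and visits, recruitment and treatment do not change. Item 3 needs a short recalculation and depends on whether the pilot recorded baseline and week-12 values for the same women, which the document does not say.

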### Randomization

2.7

As the cutoff value of LT4 supplementation based on TSH level is controversial in women who are trying to conceive, the participants will be stratified by TSH level (TSH < 2.5 mIU/L vs 2.5 mIU/L≤TSH < 5 mIU/L). Once consent has been obtained and baseline data collected, participants will be randomized to the acupuncture group (n = 142) or the the sham acupuncture group (n = 142). Randomization will be performed according to a random list of numbers generated with SPSS21.0 software (International Business Machines Corp., Armonk, NY). An independent researcher will prepare the assignments in opaque envelopes containing an allocation sequence number and take charge of the allocation sequence concealment.

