## Interventions

3

There will be 4 weeks for baseline, 12 weeks for treatment, and 1 year for follow-up in this study. Each participant will receive 36 sessions of 30-minute duration over 12 weeks (3 times per week, once every 2–3 days). Participants whose TSH is greater than 2.5mIU/L should be managed with a typical starting dose LT4 (25 ug/d). TSH levels should be optimized to <2.5 mIU/l, before conception. No additional treatment is allowed during treatment. Only licensed acupuncturists who have more than 5 years of experience will perform the treatment following the standardized operating procedures. The two groups of participants will be treated separately in different rooms to avoid communication between the participants. Each participant will take a supine position on the treatment couch which is separated by a curtain. Stick adhesive pads and disposable, sterile needles (gauge: 0.25 × 25 mm or 0.25 × 40 mm; Hwato, Suzhou, China)) will be used for acupuncture.

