### Statistical analysis

6.5

Statistical analyses of data will be performed using SPSS21.0 software (International Business Machines Corp., Armonk, NY) by professionals who will be blinded to the whole trial process. According to the principle of intention-to-treat (ITT), all randomized participants will be analyzed. Continuous variables with normal distribution will be expressed as Mean ± Standard Deviation (M ± SD) and compared by an independent sample Student *t* test. For abnormally distributed variables, they will be expressed as Medians ± Interquartile Range (MIQR) and nonparametric tests will be used. Categorical variables will be presented by frequency and percentage and analyzed by χ^2^ test or Fisher exact test. A repeated-measures multifactorial analysis will be used to analyze value changes of TPOAb, TGAb, fT3, fT4, TSH, thyroxine, AMH, FSH, LH, and E2 across 4 testing time points (See Table 1). The rest of the secondary outcomes will compare the proportions of patients with primary ovarian insufficiency and different pregnancy outcome. Safety analyses will be compared with the incidence of AEs in two groups using the χ^2^ test. Missing data will be handled by multiple imputation methods. All the tests will be two-sided, and a *P* value of less than .05 will be considered statistically significant.

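### The named two-group tests do not use the TSH stratum used in randomisation; if the stratum predicts outcome, this costs some precision, and the fix is free

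*Protocol article*

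**What the plan says.** Section 2.7 (Randomization) sets two strata: "the participants will be stratified by TSH level (TSH < 2.5 mIU/L vs 2.5 mIU/L≤TSH < 5 mIU/L". The reason given there is that the TSH cutoff for levothyroxine (LT4) is disputed in women trying to conceive. The Discussion presents stratified randomisation as a guard against bias. The stratum is linked to background treatment, because section 3 (Interventions) states: "Participants whose TSH is greater than 2.5mIU/L should be managed with a typical starting dose LT4".

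Section 6.5 (Statistical analysis) names these analyses:

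- Normal continuous variables: "Continuous variables with normal distribution will be expressed as Mean ± Standard Deviation (M ± SD) and compared by an independent sample Student" t test.
- Non-normal variables: "they will be expressed as Medians ± Interquartile Range (MIQR) and nonparametric tests will be used".
- Categorical variables: "Categorical variables will be presented by frequency and percentage and analyzed by χ^2^ test or Fisher exact test".
- Antibodies and hormones over time: "A repeated-measures multifactorial analysis will be used to analyze value changes of TPOAb, TGAb, fT3, fT4, TSH, thyroxine, AMH, FSH, LH, and E2". The factors of this analysis are not listed.
- Pregnancy outcomes and primary ovarian insufficiency (POI): a comparison of proportions between the groups, with no model named.

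Neither TSH stratum nor any other covariate is mentioned in section 6.5.

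**The concern.** An analysis should normally reflect the restrictions placed on the randomisation. When arms are balanced within strata and the stratum predicts outcome, differences between strata cannot contribute to the difference between arms. An ordinary two-sample test still counts those differences as noise. Its standard error is then larger than the true sampling error, the test rejects too rarely under the null, and some power is lost.

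It is plausible that the stratum predicts outcome here. It shares its 2.5 mIU/L cut with the LT4 rule. The Introduction and Discussion say that LT4 may slow the disease, support follicular development and improve fertility. TSH is itself a secondary outcome. What is at stake is efficiency: a benefit that the design may already have paid for and that the named tests do not credit.

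**Working it through.** **Inputs.** From section 2.6 (Sample size): pilot TPOAb 253.86 ± 178.23 (acupuncture) and 318.98 ± 201.37 IU/ml (sham), two-sided alpha 0.05, power 80%, allocation 1:1, 134 per group before dropout. Assumed, because the document gives no value: the share R² of outcome variance explained by the stratum, taken from 0 to 0.20, with equal-sized strata and exact balance of arms within each stratum.

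**Step 1: reproduce the plan's figure.**
Difference d = 318.98 − 253.86 = 65.12.
SD = √((178.23² + 201.37²)/2) = 190.15.
n = 2 × (1.960 + 0.842)² × 190.15² / 65.12², which rounds up to 134 per group. The stated figure is reproduced. It is an unadjusted calculation, so it takes no credit for the stratum.

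**Step 2: effect of ignoring the stratum.** The t test uses SE_u = 190.15 × √(2/134) = 23.23. The true standard error under exact balance is SE_t = SE_u × √(1 − R²). Hence:

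- SE ratio = 1/√(1 − R²)
- true alpha of the t test = 2 × [1 − Φ(1.96/√(1 − R²))]
- power unadjusted = Φ((d − 1.96 × SE_u)/SE_t)
- power adjusted = Φ(d/SE_t − 1.96)

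For R² = 0.10: SE_t = 22.04 and SE ratio = 1.054. Unadjusted power = Φ((65.12 − 45.53)/22.04) = Φ(0.889) = 81.3%. Adjusted power = Φ(2.955 − 1.960) = Φ(0.995) = 84.0%.

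| R² | SE too large by | True alpha, t test | Power, t test | Power, adjusted | n per group, adjusted |
|---|---|---|---|---|---|
| 0 | 0% | 0.050 | 80.0% | 80.0% | 134 |
| 0.02 | 1.0% | 0.048 | 80.3% | 80.8% | 132 |
| 0.05 | 2.6% | 0.044 | 80.7% | 82.0% | 128 |
| 0.10 | 5.4% | 0.039 | 81.3% | 84.0% | 121 |
| 0.20 | 11.8% | 0.028 | 82.7% | 88.0% | 108 |

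**Step 3: check by simulation** (20,000 trials per setting, 134 per group, balanced within two equal strata). For R² = 0.02, 0.05, 0.10 and 0.20, the t test's type I error was 0.048, 0.044, 0.037 and 0.030. A linear model with stratum stayed close to 0.05 throughout (0.049 to 0.053). Simulated power was 79.9%, 80.5%, 81.3% and 82.1% for the t test, and 80.4%, 82.0%, 83.9% and 87.4% with adjustment.

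**Step 4: what these R² values mean for TPOAb.** With equal strata, the difference in mean titre between strata that gives R² is 2 × 190.15 × √R²: 53.8, 85.0, 120.3 and 170.1 IU/ml for 2%, 5%, 10% and 20%. The two larger values are 1.8 and 2.6 times the treatment effect of 65.12. For titres, the upper rows therefore need a strong stratum effect.

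No matching table is given for the binary outcomes, because the document states no event rates for them.

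**The case against.** The strongest reply is that the article does not show the stratum being ignored where it matters most. The antibodies and hormones are assigned to a multifactorial repeated-measures analysis whose factors are unnamed. The article condenses a fuller protocol, and an unseen analysis plan may list them. This stands. A reader might infer that every outcome is analysed as if randomisation were unstratified, but the document supports that only for the simple tests it names. The reply does not help the pregnancy outcomes and POI, for which an unstratified comparison of proportions is all that is named.

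Three further stronger readings are tempting and not supported.

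- *The balance from stratifying is thrown away.* It is not. Any balance achieved still reduces the true variance of the group difference. Only the estimated standard error and the test fail to credit it.
- *The standard errors are definitely too large.* This needs a prognostic stratum and restricted allocation within strata. Section 2.7 describes a random number list and two groups of 142 but no blocking. With simple randomisation inside strata, the t test would not be conservative.
- *The loss is very large for TSH, because the stratum is baseline TSH cut in two.* Section 6.5 analyses changes in value. Where TSH is stable, change from baseline removes the stratum difference. In the upper stratum TSH is not meant to be stable, since LT4 is given with a target below 2.5 mIU/L. The same reasoning limits R² for the primary outcome where it is analysed as change from baseline, as section 2.6 defines it.

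Nor is 1/(1 − R²) the right measure of extra sample size, because under exact balance the unadjusted difference already has the smaller variance. At 80% power the ratio is ((1.96/√(1 − R²) + 0.84)/2.80)², which is 1.04 at R² = 5% and 1.08 at 10%.

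**Conclusion.** The point holds as a modest matter of efficiency. The t, nonparametric, chi-square and Fisher tests in section 6.5 do not use the stratum set in section 2.7, and the repeated-measures analysis does not say whether it does. If the stratum predicts outcome and arms are balanced within strata, the cost for a continuous outcome at 134 per group is about 0.5 to 5 percentage points of power for R² of 2% to 20%, and nothing at R² = 0. R² is assumed throughout.

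The error is on the safe side. Type I error is not inflated, the group difference is not biased, and power at 134 per group does not fall below the planned 80%, because the sample size was itself calculated without adjustment. The clearest case is the binary outcomes, where no other analysis is named. The size of the loss there cannot be given from the document.

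**What to change.** Amend section 6.5, or confirm in the analysis plan before unblinding, as follows:

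- State that TSH stratum as randomised is a fixed factor in the repeated-measures model for antibodies, thyroid hormones and ovarian hormones.
- Replace the simple two-group tests of continuous outcomes with a linear model including stratum, or with the van Elteren test where a rank method is needed.
- For pregnancy, pregnancy loss, live birth and POI, use Cochran-Mantel-Haenszel or logistic regression with stratum. Choose one in advance and name its effect measure.

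The cost is a few lines of wording. The stratum must be known at randomisation, so no new data, visits or participants are needed. Fixing it in advance also prevents a later choice between adjusted and unadjusted results.

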### Blinding

2.8

Due to the specific nature of the intervention, blinding will be maintained for participants, the data collection researcher, and the statistician except for the acupuncturist. The acupuncturist, the data collection researcher, and data analysts are not allowed to exchange information.

## Interventions

3

There will be 4 weeks for baseline, 12 weeks for treatment, and 1 year for follow-up in this study. Each participant will receive 36 sessions of 30-minute duration over 12 weeks (3 times per week, once every 2–3 days). Participants whose TSH is greater than 2.5mIU/L should be managed with a typical starting dose LT4 (25 ug/d). TSH levels should be optimized to <2.5 mIU/l, before conception. No additional treatment is allowed during treatment. Only licensed acupuncturists who have more than 5 years of experience will perform the treatment following the standardized operating procedures. The two groups of participants will be treated separately in different rooms to avoid communication between the participants. Each participant will take a supine position on the treatment couch which is separated by a curtain. Stick adhesive pads and disposable, sterile needles (gauge: 0.25 × 25 mm or 0.25 × 40 mm; Hwato, Suzhou, China)) will be used for acupuncture.

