### Secondary outcomes

6.2

The secondary outcomes include:

(1)thyroid function test including free triiodothyronine (fT3), free thyroxine (fT4), and thyroid stimulating hormone (TSH);(2)ovarian function including Anti Mullerian Hormone(AMH), follicle stimulating hormone (FSH), luteinizing hormone (LH), and estradiol (E2);(3)pregnancy outcome including pregnancy rate (%), pregnancy losses (%), and live birth rate (%);(4)primary ovarian insufficiency (%).

The thyroid function test will be performed at the baseline, 4th, 8th, and 12th week after randomization. The ovarian function will be examined on the 2nd to 4th day of the menstrual period in the 1st month, 2nd month and 3rd month compared with baseline (-1st month). Both the pregnancy outcome and the rate of primary ovarian insufficiency will be evaluated at 6 months and 1 year after treatment.

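### TSH, fT3 and fT4 are compared in all randomised women although those with TSH above 2.5 receive levothyroxine towards a TSH goal, so an acupuncture effect may be attenuated and a pooled null result would be hard to interpret

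*Protocol article*

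**What the plan says.** All references are to the Protocol article.

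- **Eligibility (2.4) and randomisation (2.7).** Women with TSH below 5.0 mIU/L may enter. Randomisation is stratified at TSH 2.5 mIU/L, and the stated reason is the disputed cutoff for giving LT4 to women trying to conceive.
- **Co-treatment (3, Interventions).** "Participants whose TSH is greater than 2.5mIU/L should be managed with a typical starting dose LT4 (25 ug/d". The next sentence sets the goal: "TSH levels should be optimized to <2.5 mIU/l, before conception". The sentence after that rules out other treatment in the treatment period. The Discussion (7) repeats the LT4 rule for TSH above 2.5 and describes its aim as holding TSH under that value.
- **Outcome (6.2).** The first secondary outcome is "thyroid function test including free triiodothyronine (fT3), free thyroxine (fT4), and thyroid stimulating hormone (TSH", measured at baseline and weeks 4, 8 and 12.
- **Analysis (6.5).** All randomised women are analysed. "A repeated-measures multifactorial analysis will be used to analyze value changes of TPOAb, TGAb, fT3, fT4, TSH", together with the remaining hormones. Neither the TSH stratum nor LT4 use is mentioned for these outcomes.

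**The concern.** In the upper TSH stratum, the variable being compared is also the one that calls for LT4 and that LT4 is meant to bring below a set value. If TSH in both arms is steered towards the same region, there is less room for the arms to differ. fT3 and fT4 have no goal of their own, but LT4 intake can move them.

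The Introduction credits LT4 with slowing the disease and supporting follicular development, and the trial asks whether acupuncture halts or delays progression. If the pooled thyroid-function result is null, a reader cannot tell whether acupuncture did nothing or LT4 normalised both arms. The trial already holds the variable that would help separate these explanations, the randomisation stratum, but the stated analysis does not use it.

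**Working it through.** **1. Reproduce the plan's own figure.** Section 2.6 sizes the trial on TPOAb: "titers of TPOAb was 253.86 ± 178.23 IU/ml in the acupuncture group and 318.98 ± 201.37IU/ml in the sham acupuncture group", with two-sided α = 0.05, 80% power and 1:1 allocation.

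- Difference: 318.98 − 253.86 = 65.12
- Pooled SD: √[(178.23² + 201.37²)/2] = 190.15
- Standardised effect: 65.12/190.15 = 0.342
- The normal-approximation formula for two means gives 134 per group. This matches "80% power (*β* = 0.2), at least 134 patients should be enrolled in each group".
- Noncentrality at 134 per group: 0.3425 × √(134/2) = 2.80. Power = Φ(2.80 − 1.96) = 80%.

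**2. What has to be assumed.** The documents give no TSH effect, no TSH SD and no share of women above 2.5. I assume a thyroid-function comparison that would have 80% power without LT4 (noncentrality 2.80, borrowed from TPOAb), the same SD with and without LT4, and a share q on LT4 that is equal in both arms. Let m be the fraction of the acupuncture effect that LT4 removes in treated women.

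**3. Pooled comparison.** The average effect is multiplied by (1 − q·m), so power = Φ(2.80 × (1 − q·m) − 1.96).

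| Share on LT4 (q) | m = 1 (all removed) | m = 0.5 (half removed) | m = 0 (none removed) |
|---|---|---|---|
| 20% | 61% | 71% | 80% |
| 30% | 50% | 66% | 80% |
| 50% | 29% | 56% | 80% |

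Example: q = 0.3, m = 1 gives 2.80 × 0.7 = 1.96, hence 50%. With q = 0.5, m = 1 it is 2.80 × 0.5 = 1.40, hence 29%.

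**4. Would restricting to the lower stratum be better?** Take q as the share in the upper stratum, with no LT4 below it. The noncentrality is then 2.80 × √(1 − q).

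- q = 0.3: 2.34, power 65%
- q = 0.5: 1.98, power 51%

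Restriction gains power only if 1 − q·m < √(1 − q), that is m > (1 − √(1 − q))/q:

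- q = 0.3: (1 − 0.837)/0.3 = 0.54
- q = 0.5: (1 − 0.707)/0.5 = 0.59

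Under half removal, the pooled comparison (66% or 56%) is slightly more powerful than the restricted one (65% or 51%).

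**5. What a stratum-by-arm interaction can show.** With full removal in the upper stratum, the interaction has noncentrality 2.80 × √[q(1 − q)]:

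- q = 0.3: 2.80 × 0.458 = 1.28, power 25%
- q = 0.5: 2.80 × 0.5 = 1.40, power 29%

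So the stratum results should be read as estimates with confidence intervals. A non-significant interaction would not show that LT4 made no difference.

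**The case against.** **The comparison is sound as a randomised contrast.** The LT4 rule is the same in both arms, randomisation is stratified at 2.5 with LT4 in mind, and all randomised women are analysed. This stands in full. A reader might infer that the comparison is biased or confounded, but the documents do not support that. LT4 begun after randomisation because of how an arm fares would be a consequence of treatment, not a confounder. What remains is a matter of sensitivity and interpretation.

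**LT4 starts during the trial are not established.** The LT4 sentence is not limited to baseline TSH, so a reader might infer that more women would start LT4 in the arm that does worse. But section 3 goes on to bar other treatment during the treatment period, and stratification is on baseline TSH. LT4 assigned from the baseline value is a plausible reading. The text leaves this open. If LT4 is fixed at baseline, the concern about unequal starts falls away, but possible attenuation in the upper stratum remains.

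**Treatment to target within 12 weeks is not spelled out.** One starting dose is given and no titration is described, and the goal in section 3 is tied to the time before conception. A fixed dose that lowers TSH by a similar amount in both arms need not shrink the difference between them. This also stands, and it is why the m = 0 column belongs in the table.

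**Stratum terms and medication tables are usual SAP content, and the SAP is not shown.** Their absence alone would be no finding, and a multifactorial model does not exclude the stratum. The point rests on what the article does state: one method and one all-randomised population, applied to a variable that the protocol also steers.

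**Conclusion.** The point holds as one of interpretation. The pooled comparison of TSH, fT3 and fT4 estimates the effect of acupuncture when LT4 is given as needed in both arms. It may understate the effect on thyroid function without LT4, and a null result would be ambiguous.

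The size cannot be fixed from the documents. Under the assumptions in the working, with 30% or 50% of women treated, power ranges from 50% or 29% (whole effect removed) through 66% or 56% (half) to 80% (none). A reader might take the lowest figures as the expected loss and say that the effect is masked. They are the worst case for those shares. The effect in women who stay below 2.5 without LT4 is untouched.

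This is a secondary outcome. The article rests its case on delayed progression mainly on TPOAb and TGAb, for which LT4 has no target, so the point does not undermine the trial's main comparison.

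**What to change.** 1. Keep the all-randomised comparison, and state that it estimates acupuncture plus LT4 as needed against sham plus LT4 as needed.
2. For TSH, fT3 and fT4, include the randomisation stratum (TSH < 2.5 against 2.5 to < 5) and its interaction with arm in the repeated-measures model. Report the arm difference with a confidence interval within each stratum, naming the lower stratum as the one least affected by LT4. The strata are fixed before randomisation, so comparisons within them remain randomised.
3. Report LT4 starts and dose by arm.
4. Reconcile the section 3 sentences on LT4 for TSH above 2.5, the TSH goal and the bar on other treatment, so that it is clear whether LT4 may start or change during the 12 weeks. No LT4 rule is proposed here.

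Making the lower stratum the main comparison is not recommended. It gains power only if LT4 removes more than about 54% (30% treated) or 59% (50% treated) of the effect in treated women.

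The cost is analysis wording and a table of LT4 use. Stratum estimates are less precise: with 30% or 50% of women in the upper stratum, the standard error in the lower stratum grows by 1/√0.7 = 1.20 or 1/√0.5 = 1.41 relative to the pooled comparison.
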